#### Secondary objective

To determine whether routine uterine tonus assessment every 15 min in the first 2 h postpartum when performed by a SBA (midwife) compared to self-assessed by a patient, results in differences in incidence of severe PPH (≥1000 ml blood loss), differences in mean blood loss, use of additional uterotonics, use of other procedures for management of PPH (surgery, manual placenta tissue removal), blood transfusion, maternal resuscitation and maternal death.

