#### Hypothesis

It is hypothesized that there will be no difference in outcomes for the SBA-assessed group compared to the self-assessment arm.

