### Sample size calculation and justification

PPH has an incidence of approximately 11.1 % in the Ghanaian population [28]. The hypothesis of this non-inferiority RCT is that there is no difference between the two treatments. To exclude a difference of between 5 to 7.5 % with a 1-sided alpha co-efficient of 5 % at a power of 80 %, between 978 and 436 participants would have to be randomized [29]. Given resource restrictions, our sample size will be 800 women, and powered to exclude a difference of 5.53 %.

As the intervention and outcome assessment take place on the same day, we expect no loss to follow-up.

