### Statistical analysis

Descriptive statistics for participant characteristics (age, marital status, employment, education, number of previous pregnancies, number of previous deliveries (live births and still births), number of children, present pregnancy history, medical and surgical history) will be presented as frequencies and percentages for dichotomous and categorical variables, and means and standard deviations for continuous variables will be presented. Differences between treatment groups will be assessed using Student’s *t* test for continuous outcome data and the chi square test for discrete outcome data, and reported significant with a *p* value of < 0.05.

Analyses for the first and second research objectives between intervention group and outcomes will be according to intention-to-treat. Primary and secondary dichotomous, categorical and continuous outcome variables will be descriptively analyzed in an approach similar to the participant characteristics analysis.

For the blood loss-related outcomes of interest (PPH, severe PPH and mean blood loss), linear and logistic regression analysis will be used to analyze the difference between the two arms. Participant characteristics with significant differences between the two groups despite randomization will be considered confounders in a multivariate logistic or linear regression analysis. The lower limit of the 90 % confidence interval on the difference between the groups in frequency of the primary outcome will be used to assess non-inferiority for these three variables. Observations with missing outcome data will not be considered in these analyses.

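### Maternal outcomes outside the three blood-loss variables get only a chi-square test at p < 0.05 under an unrestricted no-difference hypothesis; a risk difference with an interval would be better and cheap

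*Protocol article*

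**What the plan says.** Besides mean blood loss and severe PPH, the Secondary objective lists these outcomes: "use of additional uterotonics, use of other procedures for management of PPH (surgery, manual placenta tissue removal), blood transfusion, maternal resuscitation and maternal death".

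The Statistical analysis section deals with outcomes in two layers.

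- **All outcomes.** "Primary and secondary dichotomous, categorical and continuous outcome variables will be descriptively analyzed in an approach similar to the participant characteristics analysis". The approach referred to is counts and percentages (means and standard deviations for continuous variables), with groups compared by Student's t test or "the chi square test for discrete outcome data, and reported significant with a *p* value of < 0.05".
- **Three outcomes only.** "For the blood loss-related outcomes of interest (PPH, severe PPH and mean blood loss), linear and logistic regression analysis will be used", and a limit of the 90 % confidence interval "will be used to assess non-inferiority for these three variables".

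The Hypothesis section is not confined to those three: "It is hypothesized that there will be no difference in outcomes for the SBA-assessed group compared to the self-assessment arm".

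The sample size section rests on PPH alone, at an incidence of 11.1 %: "our sample size will be 800 women, and powered to exclude a difference of 5.53" percent.

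**The concern.** For three variables the plan follows non-inferiority logic: a confidence limit shows how large a difference remains possible. For the other maternal outcomes it reverts to a difference test, although the stated expectation is still that the arms do not differ. A difference test can contradict that expectation. It cannot support it, because a non-significant result sets no bound on the excess harm that the data still allow.

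This matters most for outcomes that are likely to be rarer than PPH, because a trial sized on an 11.1 % event has little power for them. Transfusion, surgery, resuscitation and death are part of what a reader will look at to judge whether handing the check to patients is safe. A table of non-significant p-values, set beside a hypothesis of no difference, invites the wrong conclusion. The point concerns this group of outcomes only, not the decision rule for the primary outcome.

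**Working it through.** **1. The plan's own figures.** Inputs from the sample size section: PPH 11.1 % in both arms, one-sided alpha 5 %, power 80 %. Equal allocation is assumed because no ratio is stated.

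n per arm = 2p(1 − p)(z₀.₉₅ + z₀.₈₀)² / Δ², with 2 × 0.111 × 0.889 = 0.1974 and (1.645 + 0.842)² = 6.183.

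| Difference Δ | n per arm | Total | Stated total |
|---|---|---|---|
| 5 % | 489 | 978 | 978 |
| 5.53 % | 399 | 798 | 800 |
| 7.5 % | 217 | 434 | 436 |

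The figures reproduce to within two women. This supports 400 per arm and confirms that the size comes from PPH only.

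**2. Power of the stated test for the other outcomes.** The documents give no rates for them, so a range is assumed. The test is the uncorrected Pearson chi-square at two-sided 5 %, with 400 per arm:

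z = (y/400 − x/400) / √[p̄(1 − p̄) × 2/400], p̄ = (x + y)/800, significant if |z| > 1.96.

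Power is the sum of the two binomial probabilities over all count pairs (x, y) that are significant.

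| True rate, midwife arm → self-assessment arm | Power | Missed |
|---|---|---|
| 0.25 % → 0.5 % | 6 % | 94 % |
| 0.5 % → 1 % | 12 % | 88 % |
| 1 % → 2 % | 19 % | 81 % |
| 2 % → 4 % | 38 % | 62 % |
| 3 % → 6 % | 54 % | 46 % |
| 5 % → 10 % | 78 % | 22 % |
| 10 % → 20 % | 98 % | 2 % |
| 1 % → 4 % (fourfold) | 81 % | 19 % |

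Power for a doubling passes 50 % at a midwife-arm rate of about 2.8 %, roughly a quarter of the 11.1 % PPH rate.

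**3. What the p-value leaves out.** Take 4 events against 10 (1.0 % v 2.5 %).

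- Test: p̄ = 14/800 = 0.0175; z = 0.015 / √(0.0175 × 0.9825 × 0.005) = 1.62; p = 0.106.
- Newcombe 95 % interval: the Wilson limits are 0.39 % to 2.54 % for 4/400 and 1.36 % to 4.54 % for 10/400. Upper limit = 1.5 + √[(4.54 − 2.50)² + (1.00 − 0.39)²] = 3.6 points. Lower limit = 1.5 − √[(2.50 − 1.36)² + (2.54 − 1.00)²] = −0.4 points.

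Under the stated criterion this is not significant, yet the data allow up to 36 extra events per 1000 women. Likewise, 8 against 16 events gives p = 0.097.

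**4. Very sparse cells.** With 0 against 4 events the expected count is 4 × 400/800 = 2 per arm. Uncorrected Pearson gives z = 0.01 / √(0.005 × 0.995 × 0.005) = 2.005 and p = 0.045; Fisher's exact test gives p = 0.124. Which side of 0.05 the result falls on depends on an approximation used where it is poor.

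**The case against.** The strongest reply has four parts.

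- **The misreading is not in the text.** These outcomes are to be analysed descriptively, the Secondary objective asks whether differences arise, and nowhere is p > 0.05 declared to be evidence of equality. This stands. A reader might infer from the Hypothesis and Statistical analysis sections together that the trial will claim no difference in transfusion or death from a non-significant test. The documents create that risk but do not state that intention.
- **Serious harm is not left unprotected, and larger effects would be seen.** Severe PPH, a main harm measure, has the confidence-limit rule, and a rise from 1 % to 4 % would be detected about 81 % of the time. This also stands. It would be tempting to say that the test returns a non-significant result almost whatever self-assessment does; the calculation refutes that.
- **Additional uterotonics are not shown to be rare or severe.** Correct: at 5 % to 10 % power is 78 %, and at 10 % to 20 % it is 98 %. For a common outcome only the argument for an interval remains, not the argument from low power.
- **Counts are reported, so anyone can compute the interval, and such detail belongs in a fuller document.** This stands in part. No data are lost, and the choice among interval methods is detail. But the article does not leave the method open. It names a difference test and a significance threshold, and that method cannot bound excess harm. Naming a better one corrects a stated choice.

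Low power for rare secondary events is ordinary in a trial sized on a commoner outcome and is no fault in itself.

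**Conclusion.** The point holds as a cheap improvement. For the maternal outcomes outside the three-variable rule, the only stated inferential criterion is a chi-square test at p < 0.05, and non-significance on it cannot support an unrestricted expectation of no difference.

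For rare outcomes a true doubling would be missed more often than found. This rests on 400 women per arm, an uncorrected two-sided 5 % test, and midwife-arm rates below about 2.8 %, which are assumed because the documents give none. The p-value itself is also unreliable when cells are very sparse. The sample size and the handling of PPH, severe PPH and mean blood loss are not affected by this point.

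**What to change.** In the Statistical analysis section, for additional uterotonics, surgery or manual removal, transfusion, resuscitation and death:

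1. Report the risk difference, self-assessment minus midwife, with a two-sided 95 % confidence interval by a method valid for sparse data (Newcombe or exact), in place of the chi-square p-value.
2. State that the upper limit is what is interpreted, as the largest excess harm not excluded, and that p > 0.05 will not be taken as evidence of no difference.
3. If a test is kept, use Fisher's exact test where expected counts are below 5.

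In the Hypothesis section, limit the expectation of no difference, and with it any non-inferiority conclusion, to the outcomes that have a non-inferiority rule.

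The cost is two or three sentences and one table column, with no new data, patients or staff. The downside is that the report will show wide intervals and make a weaker claim about rare harms. The change does not raise power; it shows what the data can and cannot exclude.

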## Background

### Postpartum hemorrhage is the leading cause of maternal death

Each year, approximately 287,000 women die because of preventable causes related to pregnancy and childbirth [1]. Almost all (99 %) of these deaths occur in low-income and middle-income countries (LMIC), with the largest burden in sub-Saharan Africa and South Asia [1].

The most common cause of maternal death is postpartum hemorrhage (PPH), defined as blood loss equal to or greater than 500 ml within 24 h after birth of the infant. PPH occurs in around 10.5 % of all deliveries and is responsible for more than 130,000 deaths annually [2, 3]. In sub-Saharan Africa, 33.9 % of maternal deaths are due to PPH [4].

The maternal mortality ratio of Ghana in 2013 was 380 maternal deaths per 100,000 live births [5]. The leading cause of maternal deaths was obstetric hemorrhage, with estimates ranging between 27 and 32 % [6–10].

Causes of PPH include uterine atony, uterine rupture, incisions, lacerations and coagulopathy, with uterine atony being the most common cause of PPH. Risk factors for atony include multiparity (five or more deliveries), polyhydramnios, fetal macrosomia, abnormal placentation, placental abruption, induced or prolonged labor and retained placental tissue [2, 11].

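### Covariates for the blood-loss regressions are chosen by significant baseline differences, so chance imbalance rather than prognostic value sets the adjusted model

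*Protocol article*

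**What the plan says.** All of the analysis text is in the protocol article, Statistical analysis.

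- Group comparisons use the t test or chi-square test and are "reported significant with a *p* value of < 0.05". This sentence closes the paragraph on participant characteristics, although its wording refers to outcome data.
- The characteristics run from age and marital status to "number of children, present pregnancy history, medical and surgical history".
- For the three blood-loss outcomes, "linear and logistic regression analysis will be used to analyze the difference between the two arms".
- The covariate rule follows: "Participant characteristics with significant differences between the two groups despite randomization will be considered confounders in a multivariate logistic or linear regression analysis". No covariate is fixed in advance.
- The next sentence says that a limit of the "90 % confidence interval on the difference between the groups in frequency of the primary outcome will be used to assess non-inferiority", and applies this to all three blood-loss outcomes.

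The Background names factors that matter for the outcome: "Risk factors for atony include multiparity (five or more deliveries", and the list goes on to include induced or prolonged labour. The number of previous deliveries is among the data to be collected (Other study endpoints and parameters). None of these factors is named as a covariate.

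**The concern.** A p value for a baseline difference between randomised arms tests a hypothesis that valid randomisation already makes true. It measures how unlucky the allocation was on that variable, not how strongly the variable predicts bleeding. Under the stated rule, marital status at p = 0.04 enters the model and number of previous deliveries at p = 0.06 does not.

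Three things follow:

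- The adjusted model is known only after the data are seen.
- Precision available from a known predictor is usually given up.
- In logistic regression the conditional odds ratio depends on which covariates are included, so a data-chosen model changes what is estimated as well as how precisely.

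Because the non-inferiority sentence directly follows the covariate rule, a crude and an adjusted estimate are both candidates for the deciding interval. Care providers and research assistants are not blinded (Randomization, treatment allocation, and treatment concealment), so it is better not to leave that choice open.

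**Working it through.** **1. Sample size, reproduced first.** Inputs from Sample size calculation and justification: "PPH has an incidence of approximately 11.1 % in the Ghanaian population", a "1-sided alpha co-efficient of 5" %, and power 80 %. Equal allocation is assumed. The formula per arm is n = (1.645 + 0.842)² × 2 × 0.111 × 0.889 / margin².

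| Margin | Per arm | Total | Stated total |
|---|---|---|---|
| 5 points | 489 | 978 | 978 |
| 7.5 points | 217 | 434 | 436 |
| 5.53 points | 399 | 798 | 800 |

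With 400 per arm the margin is 5.52 points. The stated figures reproduce within rounding, and nothing in this point changes the sample size.

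**2. Chance that at least one covariate enters.** For k independent tests at 0.05 with no true difference, the chance is 1 − 0.95^k. The section lists nine headings if medical and surgical history count as one.

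| Effective tests k | 1 − 0.95^k |
|---|---|
| 5 | 23 % |
| 7 | 30 % |
| 9 | 37 % |
| 12 | 46 % |
| 15 | 54 % |

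The right k is uncertain in both directions. Previous pregnancies, previous deliveries and number of children are strongly related; counting them as one gives 9 − 2 = 7. The history headings may each hold several variables, which pushes k up.

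**3. Chance that a given prognostic factor is left out.** Each characteristic is selected with probability 0.05, whatever its prognostic strength, so it is omitted with probability 1 − 0.05 = 0.95.

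**4. Effect on the non-inferiority conclusion.** This was simulated with 8,000 trials per scenario, 400 women per arm, nine independent covariates of which one is prognostic, an 11.1 % event rate and a 5.53-point margin. The model was linear for the risk difference, with robust standard errors. The covariate effects are assumptions; the article gives none.

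| Assumed log OR per SD | Quantity | Unadjusted | Pre-specified | Selected by significance |
|---|---|---|---|---|
| 0.5 | Power, true difference 0 | 79.5 % | 80.0 % | 79.4 % |
| 1.0 | Power, true difference 0 | 79.7 % | 82.8 % | 80.3 % |
| 0.5 | One-sided error at the margin | 5.3 % | 5.2 % | 5.2 % |
| 1.0 | One-sided error at the margin | 5.2 % | 5.3 % | 5.0 % |

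At least one covariate was selected in 36 to 38 % of simulated trials, and the prognostic one in about 5 %, in line with steps 2 and 3. The power cost of selection against pre-specification is 80.0 − 79.4 = 0.6 points and 82.8 − 80.3 = 2.5 points. The Monte Carlo standard error of each power figure is √(0.8 × 0.2 / 8000) = 0.45 points. The smaller gap should therefore not be leaned on.

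**The case against.** **The crude difference may be what decides.** The interval is described as one on a difference in frequency. That most naturally means the simple difference between arms, whereas a logistic model yields an odds ratio. On that reading the adjusted regressions are supplementary. This stands. A reader might infer that the significance rule picks the model on which non-inferiority is judged, but the text does not say so. It does not exclude it either: the two sentences are adjacent and cover the same three outcomes. Which estimate is primary could also be settled in a fuller document, so that silence alone is not the point. The stated selection rule is.

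**The 37 % is not firm.** It assumes nine independent tests, and it is the chance that some covariate enters, not the chance of a wrong conclusion. Both remarks stand, so only a range is given.

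**The harm is small.** This stands too. The exclusion criteria already remove women with an earlier PPH, a palpable fibroid or bleeding before delivery, which takes out some prognostic variation. High parity and induced or prolonged labour are not excluded and remain.

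**Imbalance might not be pure chance.** Women can be excluded and replaced because of complications after allocation. A 0.05 screen would not reliably detect or correct the result of that, so it does not rescue the rule.

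**Conclusion.** The point holds as a failure of pre-specification in a rule that the article states. Chance imbalance determines which covariates enter the adjusted blood-loss models. There is roughly a 23 to 54 % chance that at least one enters, and about a 95 % chance that any given prognostic factor does not. The first figure rests on 5 to 15 effective independent tests, the second on valid randomisation.

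Two stronger readings are tempting and are not supported. One is that the rule inflates the non-inferiority error rate: simulated error stayed at about 5 % under all three approaches. The other is that the primary model would change in over a third of trials: that needs both nine independent tests and an adjusted primary analysis, and the article establishes neither. The loss of precision is probably modest, 0.6 to 2.5 power points under assumed effects. The rule should be changed because it is avoidable and cheap to correct; it does not invalidate the trial.

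**What to change.** - Replace the covariate sentence with a short list fixed in advance and used whatever the observed balance: number of previous deliveries, age, and any present-pregnancy risk factor confirmed as recorded. The article lists present-pregnancy history only in general terms, so induction should not be named until its recording is confirmed.
- Stop using baseline significance tests to select covariates. Edit the t-test and chi-square sentence rather than delete it, because its wording also covers outcome data and the outcome analysis refers back to that approach. The planned outcome comparisons should stay.
- State that one risk difference with its 90 % confidence interval decides non-inferiority. Either the pre-specified adjusted difference, obtained for example by standardisation from the logistic model, or the unadjusted difference will do; the other becomes the sensitivity analysis. Both remove the data dependence.

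The cost is wording in the protocol or analysis plan, settled before outcomes are examined by arm. The sample size does not change. No new data are needed if the list is confined to variables confirmed as recorded.

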**Methods and Design:**

The study is an individual-level two-arm non-inferiority randomized controlled trial (RCT). A total of 800 women will be recruited in Korle Bu Teaching Hospital in Accra, Ghana. Adult women in labor at term with an expected vaginal delivery who received antenatal instructions for self-assessment of uterine tonus will be eligible for inclusion. Women with an increased risk for PPH will be excluded. Women will be randomized to uterine tone assessment by a skilled birth attendant (midwife) or uterine tone self-assessment (with the safety back-up of a midwife present in case of PPH or uterine atony). Postpartum blood loss will be measured through weighing of disposable mats. The main study endpoints are PPH (≥500 ml blood loss), severe PPH (≥1000 ml blood loss), mean blood loss, and routine maternal and neonatal outcomes. Participants and caregivers will not be blinded given the nature of the intervention.

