### Study objectives and hypothesis

#### Primary objective

To determine whether there is a difference in incidence of PPH (≥500 ml blood loss) following routine uterine tone assessment every 15 min in the first 2 h postpartum performed by a SBA (midwife) compared to self-assessment by a patient.

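### The non-inferiority criterion set for the primary outcome, PPH, is extended to severe PPH and mean blood loss with no testing order and no margin, so either could be declared non-inferior after PPH has failed

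*Protocol article*

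**What the plan says.** All places are in the Protocol article.

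- **Primary objective:** a single outcome, "To determine whether there is a difference in incidence of PPH (≥500 ml blood loss").
- **Secondary objective:** severe PPH (≥1000 ml) and mean blood loss are listed here, with additional uterotonics, procedures, transfusion, resuscitation and maternal death.
- **Sample size calculation and justification:** the calculation uses PPH only. "PPH has an incidence of approximately 11.1 % in the Ghanaian population", and the numbers are derived "with a 1-sided alpha co-efficient of 5 % at a power of 80" %. The result is "our sample size will be 800 women, and powered to exclude a difference of 5.53" %. No other outcome has a margin.
- **Statistical analysis:** PPH, severe PPH and mean blood loss are grouped as the blood-loss outcomes. One limit of the 90 % confidence interval for the between-group difference in frequency of the primary outcome "will be used to assess non-inferiority for these three variables".
- **Abstract, Methods and Design:** "The main study endpoints are PPH (≥500 ml blood loss), severe PPH (≥1000 ml blood loss), mean blood loss, and routine maternal and neonatal outcomes", with no separation of primary from secondary.

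**The concern.** The objectives and the sample size treat PPH as the outcome that decides the trial. The analysis section then gives two secondary outcomes the same decision rule at the same one-sided 5 %. It does not say whether they are looked at only after PPH has succeeded, or whether they are supportive.

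What is left open is the case where PPH does not meet non-inferiority. As written, severe PPH or mean blood loss could still be declared non-inferior. In a trial of handing a safety check from the midwife to the patient, such a claim could be read as support for self-assessment despite a failed primary outcome.

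The missing margins make this worse. The criterion is worded as a difference in the frequency of the primary outcome. It does not fit a mean in millilitres at all, and for severe PPH it leaves the PPH figure as the only one at hand.

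**Working it through.** **1. Does the plan's 5 % belong to PPH alone?**

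Inputs from the sample size section: PPH rate 11.1 % in both arms, one-sided 5 %, power 80 %. Equal allocation is assumed, since the ratio is not stated.

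n per arm = 2p(1−p)(z₀.₉₅ + z₀.₈₀)² / margin²

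2 × 0.111 × 0.889 = 0.19736, and (1.6449 + 0.8416)² = 6.1826.

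| Margin (points) | n per arm | Total | Article |
|---|---|---|---|
| 5 | 488.1, so 489 | 978 | 978 |
| 7.5 | 216.9, so 217 | 434 | 436 |
| 5.53 | 399.0, so 399 | 798 | 800 |

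With 400 per arm the margin is √(0.19736 × 6.1826 / 400) = 5.52 points, against 5.53 in the article. One-sided 2.5 % would have needed 1240 and 552 for the first two rows. The article's "between 978 and 436 participants would have to be randomized" therefore reflects one PPH comparison at one-sided 5 %, which agrees with the use of a 90 % interval. For PPH the design is consistent.

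**2. Chance of at least one false claim among three**

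Assumptions, none of them in the article:
- each true difference lies exactly at that outcome's own margin;
- each is assessed at one-sided 5 %;
- the three test statistics are jointly normal with a common correlation ρ.

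P(at least one) = 1 − P(Z₁ < 1.645, Z₂ < 1.645, Z₃ < 1.645). At ρ = 0 this is 1 − 0.95³ = 14.3 %.

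**3. Chance that PPH fails while another outcome passes**

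This is P(at least one) − P(PPH passes) = P(at least one) − 5 %.

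| ρ | At least one false claim | PPH fails, another passes |
|---|---|---|
| 0 | 14.3 % | 9.3 % |
| 0.4 | 12.5 % | 7.5 % |
| 0.5 | 11.8 % | 6.8 % |
| 0.6 | 11.1 % | 6.1 % |
| 0.8 | 9.3 % | 4.3 % |
| 0.9 | 8.0 % | 3.0 % |

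**4. Less arbitrary correlations**

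Assume log-normal blood loss with 11.1 % at or above 500 ml and 0.5 to 5 % at or above 1000 ml. The implied correlations are 0.20 to 0.65 (PPH with severe PPH), 0.49 to 0.76 (PPH with mean loss) and 0.38 to 0.72 (severe PPH with mean loss). The any-of-three rate is then 10.6 to 11.8 %, so PPH fails while another passes in 5.6 to 6.8 %.

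**5. What happens if the PPH margin is borrowed for severe PPH?**

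The severe PPH rates here are assumed for illustration. With 400 per arm, a 90 % interval (Wald, exact binomial probabilities) and 5.53 points as the margin, a true doubling from 2 % to 4 % would be declared non-inferior about 89 % of the time. A doubling from 1 % to 2 % would be declared non-inferior more than 99 % of the time. The PPH margin cannot serve for the rarer outcome.

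**The case against.** The strongest reply is that the article does rank its outcomes. PPH is the only primary objective, severe PPH and mean blood loss sit under the secondary objective, the sample size rests on PPH, and the criterion sentence itself speaks of the primary outcome in the singular. Nowhere is success on any one of the three said to establish the trial's conclusion. All of this stands. A reader might infer that the plan has no hierarchy, or that its error rate is 11 to 12 % where 5 % is stated. The documents do not support either: the stated 5 % is attached to PPH and is correct for PPH.

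It also stands that the any-of-three rate is conditional. It needs a correlation that the article does not give and all three differences exactly at their margins, two of which do not exist in the text.

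A reader might further infer inflated error from the other secondary outcomes, because group differences are "reported significant with a *p* value of < 0.05". That does not hold either. The same section says that the outcome variables are analysed descriptively, and tests of difference add nothing to a false non-inferiority rate.

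Finally, multiplicity for secondary outcomes may be handled in the full protocol or the statistical analysis plan, neither of which is shown. That would answer a complaint of silence. This point concerns a rule the article does state, and a later document would have to qualify it. Naming PPH as primary does not settle what may be claimed on the other two if PPH fails.

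**Conclusion.** The point holds in a limited form. The conclusion on PPH keeps its one-sided 5 %. What is not controlled is the set of non-inferiority claims that the analysis section allows, because two secondary outcomes share the primary's criterion without an order and without margins.

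If each outcome lay at its own margin, at least one false claim would arise in roughly 8 to 14 % of trials for correlations from 0.9 down to 0. A claim on another outcome after PPH has failed would arise in about 3 to 9 %. These are illustrations under the assumptions listed, and they are not error rates of the trial's primary conclusion. The missing margins are the firmer part of the defect, since without them a false claim on severe PPH or mean blood loss is not even defined.

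**What to change.** In the Statistical analysis section, state that the non-inferiority conclusion rests on PPH (≥500 ml) alone at one-sided 5 %. Then choose one of two routes:

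- **Fixed sequence.** Assess severe PPH only if PPH has met non-inferiority, and mean blood loss only if severe PPH has as well. Each is tested at one-sided 5 % against its own margin, stated in advance (in percentage points for severe PPH, in millilitres for mean blood loss).
- **Supportive only.** Report severe PPH and mean blood loss as estimates with confidence intervals and make no non-inferiority claim on them.

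In the abstract, name PPH as primary and the rest as secondary, to match the objectives.

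The cost is wording, plus justifying two margins if the first route is taken. No extra women or data are needed, and PPH keeps its full alpha and power. The one real loss is that severe PPH and mean blood loss can no longer support a stand-alone non-inferiority claim.

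### The non-inferiority criterion, defined on the frequency of PPH, is also applied to severe PPH and mean blood loss, two secondary outcomes that it does not fit.

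*Protocol article*

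**What the plan says.** The Primary objective is the incidence of PPH, at a threshold of 500 ml. The Secondary objective lists, among other outcomes, "differences in incidence of severe PPH (≥1000 ml blood loss), differences in mean blood loss".

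The Statistical analysis section groups three outcomes: "For the blood loss-related outcomes of interest (PPH, severe PPH and mean blood loss), linear and logistic regression analysis will be used" to compare the arms. It then sets the decision rule for non-inferiority: "The lower limit of the 90 % confidence interval on the difference between the groups in frequency of the primary outcome will be used to assess" this. Its scope is explicit, since the limit "will be used to assess non-inferiority for these three variables".

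That section states no margin. The figures that could serve as one are in Sample size calculation and justification: a range of 5 to 7.5 %, and the statement that 800 women make the trial "powered to exclude a difference of 5.53" %. Both rest on one planning rate: "PPH has an incidence of approximately 11.1 % in the Ghanaian population". The article gives no rate or margin for severe PPH and no margin in millilitres.

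**The concern.** A non-inferiority conclusion needs an interval for the outcome in question and a margin in that outcome's units, set with its expected level in mind. The rule supplies these for PPH at most. Severe PPH is a subset of PPH and so is rarer, and mean blood loss is continuous.

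The stake is what the trial may conclude. A report that follows the text could call self-assessment non-inferior on severe PPH, its most serious blood-loss outcome, and on mean blood loss, by a criterion that was not set for either.

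**Working it through.** **Inputs.** From the article: PPH rate 11.1 %, one-sided alpha 5 %, power 80 %, 800 women, differences of 5, 5.53 and 7.5 points. Assumed: 1:1 allocation (400 per arm), equal PPH rates under the planning hypothesis, and a confidence limit taken on the side unfavourable to self-assessment. Also assumed, because the article gives none: a severe PPH rate of 1 to 5 % with midwife assessment.

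**Step 1: what the 5.53 points belong to.** n per arm = (1.645 + 0.842)² × 2 × 0.111 × 0.889 / margin².

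| Margin (points) | Total N, recomputed | Total N, stated |
|---|---|---|
| 5 | 978 | 978 |
| 5.53 | 798 | 800 |
| 7.5 | 434 | 436 |

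The figures reproduce to within 2 women. So 5.53 points is specific to PPH at 11.1 %: it allows a rise to 16.6 %, a ratio of (11.1 + 5.53)/11.1 = 1.50.

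**Step 2: literal reading.** The PPH interval alone decides all three outcomes. With PPH at 11.1 % in both arms, SE = √(2 × 0.111 × 0.889/400) = 0.0222, and the probability of passing is Φ(0.0553/0.0222 − 1.645), about 80 %.
- If self-assessment moves women from 500–999 ml to ≥1000 ml, the PPH rate does not change. The probability stays at 80 % however many women move.
- If the extra severe cases are also extra PPH cases, it falls to about 64 % for +1 point and 45 % for +2 points, but only because PPH itself rose.

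Severe PPH and mean blood loss play no part of their own in the decision.

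**Step 3: alternative reading, mean blood loss.** The outcome's own interval is in millilitres and the limit is in percentage points. The two cannot be compared, so there is no rule. This needs no assumed rate.

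**Step 4: alternative reading, severe PPH.** Its own interval is compared with 5.53 points. For a rate p with midwife assessment and a true risk ratio r:
- allowed relative risk = (p + 0.0553)/p
- P(pass) = Φ( [0.0553 − (r − 1)p] / √{[p(1 − p) + rp(1 − rp)]/400} − 1.645 )

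Example, p = 2 % and r = 2: SE = √{(0.02 × 0.98 + 0.04 × 0.96)/400} = 0.01204; (0.0553 − 0.02)/0.01204 = 2.93; Φ(2.93 − 1.645) = 90 %.

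| Assumed rate | Allowed relative risk | P(pass), true doubling | P(pass), true tripling |
|---|---|---|---|
| 1 % | 6.5 | >99.9 % | 97 % |
| 2 % | 3.8 | 90 % | 30 % |
| 3 % | 2.8 | 53 % | 3 % |
| 4 % | 2.4 | 23 % | <1 % |
| 5 % | 2.1 | 9 % | <1 % |

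Whatever the rate, as long as it is below 11.1 %, the margin is larger relative to severe PPH than to PPH. Below 5.53 % it permits more than a doubling.

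**Step 5: as counts, same reading.** Severe PPH in 4 v 18 women (of 400 each) gives an upper 90 % limit of 3.50 + 1.645 × 1.150 = 5.39 points; 8 v 21 gives 3.25 + 1.645 × 1.317 = 5.42 points. Both pass. The chi-square test planned in the same section gives p of about 0.002 and 0.014 (uncorrected). A result can formally be both significantly worse and non-inferior, but here the observed ratios are 4.5 and 2.6.

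**The case against.** The strongest reply is that the sentence is loosely worded and little hangs on it. Both outcomes are secondary and are framed as differences. The same section plans t tests, chi-square tests and regression for them, so estimates, including one in millilitres, would be produced anyway. The article is a condensed text, and the full protocol is available on request. Most of this stands and bears on the grade. It does not remove the point: the article does not leave the rule for these outcomes open. It states one and names what it covers.

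A reader might infer more than the documents support:

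- *That the trial would pass self-assessment on severe PPH even if the rate doubled or tripled.* Not in general. The figures in Step 4 apply only to the second reading and an assumed rate. A tripling passes with 30 % probability at 2 % and 3 % at 3 %; a doubling passes with 9 % at 5 %. Under the literal reading the relevant figures are those in Step 2.
- *That 5.53 points is the declared margin for severe PPH.* It is not. The article ties it to PPH and to 800 women, says only that the trial is powered to exclude it, and does not repeat it in the analysis section.
- *That the margin is several times the severe PPH rate.* This depends on the rate: 5.53 points is 5.5 times a rate of 1 %, 1.8 times 3 % and 1.1 times 5 %. Only the weaker statement, relatively laxer than for PPH, holds without an assumed rate.
- *That missing secondary margins are an error in themselves.* An article may leave them to the full protocol. The error is in the rule it does state.

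**Conclusion.** The point holds as a defect in a stated rule. The criterion on PPH frequency is not valid for severe PPH or mean blood loss on either reading. Literally, it ignores their data. On the alternative, it has no meaning in millilitres and is relatively laxer for severe PPH than for PPH. These conclusions need no assumed rate.

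How lax it is for severe PPH does depend on the assumed 1 to 5 %, on 400 per arm and on 5.53 points serving as the margin. Within that range, the allowed relative risk runs from 6.5 down to 2.1, and the chance of passing a true doubling from above 99.9 % down to 9 %.

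The primary PPH analysis and the sample size are untouched. Since only secondary outcomes are concerned, this should be corrected but ranks below a must-fix.

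**What to change.** Amend the Statistical analysis section so that the non-inferiority conclusion is confined to PPH ≥500 ml. Report severe PPH as a risk difference and a risk ratio, and mean blood loss as a difference in millilitres, each with a confidence interval and no non-inferiority conclusion.

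If a non-inferiority claim is wanted for either, pre-specify a justified margin in that outcome's own units (percentage points or a ratio for severe PPH, millilitres for mean blood loss) and judge it on that outcome's own interval.

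The cost is wording. Sample size and data collection do not change. Under the first option, two non-inferiority claims on secondary outcomes are given up.
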